## Abstract

**Background:**

In Kenya, 65% of sexually active unmarried women use modern contraceptives, a population at increased risk of HIV acquisition compared to other populations. Anchoring HIV prevention services, including pre-exposure prophylaxis (PrEP), to trusted contraceptive delivery settings offers opportunities to efficiently reach this important population. In Kenya, almost half (40%) of women accessing contraception services do so outside traditional healthcare facilities, such as retail pharmacies. Thus, integrating PrEP services into retail pharmacies may increase options for reaching adolescent girls and young women (AGYW) who could benefit from PrEP. Efforts are underway to define care pathways for pharmacy-delivered PrEP services in Kenya, including unsupported and supported models with nurse navigators.

**Methods:**

The AGYW Pharmacy PrEP study is an unblinded 2-arm cluster-randomized controlled trial in Kisumu, Kenya. The objective is to determine the effect that unsupported versus supported pharmacy-delivered PrEP services has on PrEP initiation, persistence, and adherence among AGYW seeking contraception. Twenty retail pharmacies offering pharmacy provider-led PrEP delivery will be randomized 1:1 to either receive or not receive a nurse navigator to support PrEP delivery. Eligible AGYW (*n* = 1900 total, *n* = 950/arm) will be ≥ 15 years old, purchasing a method of contraception at the pharmacy. Trained pharmacy provider will offer eligible AGYW either daily oral PrEP or the monthly DPV vaginal ring. The primary trial outcomes are PrEP initiation (use of PrEP at 1 month), persistence (use of PrEP at 10 months), and adherence (quantified by levels of TFV or DPV in hair samples). Additionally, several secondary (STI incidence, PrEP method selection, predictors of PrEP adherence) and exploratory outcomes (HIV incidence, quality of care, contraceptive method mix) will be explored.

**Discussion:**

We hypothesize pharmacy-delivered PrEP services supported with nurse navigator, versus delivered by pharmacy providers alone, will improve PrEP outcomes among AGYW seeking contraception. Our results will help policy makers better understand how to potentially implement this novel differentiated service model for PrEP and prime pharmacies for the delivery of new PrEP agents in the pipeline (e.g., long-acting injectables and multi-purpose technologies). The study was initiated on May 13, 2023, and is expected to be completed by February 2025.

**Trial Registration:**

ClinicalTrials.gov (NCT05467306), with registration on July 20, 2022.

## Introduction

### Background and rationale 

In Kenya, 65% of unmarried sexually active women use modern contraceptives [1] and may benefit from engagement in HIV prevention services, including pre-exposure prophylaxis (PrEP) with daily oral pills or the monthly dapivirine vaginal ring (DPV-VR). Anchoring PrEP service delivery to settings women already trust and routinely access for contraception may help reach adolescent girls and young women (AGYW), who are at risk of HIV acquisition in Kenya. In Kenya, almost all PrEP service delivery occurs through public health clinics; however, almost half (40%) of women access contraception outside clinics including at retail pharmacies [1]. Thus, implementing novel models of PrEP delivery that operate outside traditional clinic settings to reach AGYW who do not frequently attend public clinics can help maximize the potential impact of PrEP[2].

Delivery of PrEP at retail pharmacies is a promising strategy to expand PrEP coverage. Compared to public clinics, retail pharmacies are often more accessible, as they are ubiquitous and typically located in high-traffic areas [3–5]. Additionally, services delivered at pharmacies may be more private and confidential than those delivered at public clinics, as individuals often visit pharmacies for a variety of reasons unrelated to their healthcare needs [6–8]. Pharmacies may also be more responsive to client demands compared to public clinics, as they are typically self-sustained via fee-for-service care and thus have a vested interest in satisfying customers for sustained and repeat client engagements [9–12]. Several formative qualitative studies and pilot studies on pharmacy-delivered PrEP services, mainly conducted in Kenya and South Africa, have found that this novel model of PrEP delivery is feasible, acceptable, and preferred by pharmacy clients, including AGYW [13–16].

One pharmacy-delivered PrEP services model tested in these pilots entailed a nurse navigator stationed at a retail pharmacy who facilitated PrEP delivery for AGYW seeking contraception [15, 16]. In this pilot, Kenyan AGYW (*n* = 235) offered daily oral PrEP at two retail pharmacies frequently initiated (85%), planned to continue using (68%), and were willing to pay for PrEP services (69%), even when these were available for free at public clinics—suggesting sustainability of this approach [15]. Participants cited convenience, short wait times, less stigma, and high-quality counseling on PrEP and family planning services by the nurse navigators at the pharmacies as their reasons for preferring pharmacy- versus clinic-based PrEP services [17, 18].

In this cluster-randomized controlled trial (cRCT) in Kenya, we will determine the additional benefit (i.e., effect) of stationing a nurse navigator at retail pharmacies to support pharmacy-delivered PrEP services (versus pharmacy-delivered PrEP services without a nurse navigator) on PrEP initiation, persistence, and adherence among AGYW seeking contraception.

### Objectives 

We aim to determine the effect of nurse navigators on PrEP initiation, persistence, and adherence among HIV-negative AGYW (age 15–24 years) seeking contraception by comparing pharmacy-based PrEP delivery models with and without nurse navigators.

### Trial design 

This is a two-arm, unblinded, cluster-randomized controlled trial in which 20 retail pharmacies offering standard PrEP delivery are randomized 1:1 to either receive or not receive a nurse navigator to support PrEP delivery for AGYW.

## Methods: participants, interventions, and outcomes

### Study setting 

The study will be conducted in Kisumu County, Kenya, where HIV prevalence is 21% among cisgender women [17, 18]. We conducted a landscape analysis of the 119 retail pharmacies in Kisumu to gather information on the types of customers who attend, services offered (e.g., HIV testing), and products purchased (e.g., contraceptive methods) at pharmacies as well as the availability of a separate, private consultation room. Based on this assessment, we selected 20 retail pharmacies that met study criteria: were willing to provide PrEP services per the national guidelines [19], had a separate consultation room for HIV testing and PrEP counseling, and provided a variety of contraceptives to AGYW clients, including emergency contraception, oral contraceptive pills, injectables, implants, and condoms (Fig. 1).

**Fig. 1 Fig1:**
[figure not shown]
Distribution of study sites in Kisumu County, Kenya [20]

### Eligibility criteria 

All participants are screened for eligibility and asked to provide oral and written informed consent before study participation. At screening, eligibility information is obtained. The results from the screening assessments are reviewed for the inclusion/exclusion criteria described below:

InclusionFemale genderSeeking contraception (EC, OCP, injectables, implants, and condoms) from the retail pharmacy siteAge between > 14 and < 25 years oldWillingness to receive PrEP screening per national guidelines including HIV testingNot currently taking PrEPAble and willing to provide informed consent for participation

ExclusionMale genderNot seeking contraception (EC, OCP, injectables, implants, and condoms) from the retail pharmacy siteAge < 15 or > 24 years oldNot willing to receive PrEP screening per national guidelines or not willing to receive HIV testingCurrently taking PrEPNot able or willing to provide informed consent for participation

### Who will take informed consent? 

All potential participants are screened for eligibility and then asked to provide oral and written informed consent by a trained study team member before study participation. The parental consent will be waived for AGYW aged 15–17 years. This waiver is based on the recommendations of the Ministry of Health’s Guidelines for Conducting Adolescent HIV Sexual and Reproductive Health Research in Kenya (2015) [21]. According to the Kenya Ministry of Health guidelines, adolescents are able to provide consent for HIV and STIs testing and treatment in Kenya and therefore parental consent can be waived for HIV/STI related studies.

### Additional consent provisions for collection and use of participant data and biological specimens 

The study provides information on specimen collection during enrollment. Specimen collection is not performed unless informed signing of the study consent form is confirmed. In addition to consenting to participate in the study, participants opt in or out of agreeing to store samples at the Kisumu site and the University of Washington for future research into HIV, HIV-related diseases, STIs, and other infectious diseases.

## Interventions

### Explanation for the choice of comparators 

An information-motivation-behavioral skills (IMB)-guided approach informed the development of the nurse navigator model for pharmacy-based PrEP delivery tailored to AGYW, using quantitative and qualitative data from the pilot (Fig. 2) [15, 22]. The nurse navigator model is designed to target domains of the IMB (PrEP adherence information, PrEP adherence motivation, PrEP behavioral skills, PrEP adherence behavior and health outcome). Nurse navigators expand PrEP support for AGYW and provide opportunities for dialogue beyond PrEP, enabling AGYW to receive counseling on contraception, relationships, and other concerns across IMB domains, which may facilitate PrEP use.

**Fig. 2 Fig2:**
[figure not shown]
Information-motivation-behavioral skills model for PrEP adherence (adapted from Fisher 2006 and Ferrer et al. 2010). AGYW, adolescent girls and young women; HIV, human immunodeficiency virus; PrEP, pre-exposure prophylaxis

To our knowledge, this pilot was the first evaluation of a pharmacy PrEP delivery tailored to AGYW and our nurse navigator model addressed issues specific to AGYW in the context of contraception. Our pilot results provided a signal to formally test nurse navigators as a strategy to improve PrEP outcomes among AGYW in a rigorous cluster randomized clinical trial with a comparison group of standard pharmacy-based PrEP without nurse navigators.

### Intervention description 

In both arms, AGYW receive standard PrEP services at the pharmacy, which entail a pharmacy provider using a prescribing checklist to identify individuals with risk for HIV acquisition and at low risk of any drug contraindications, counsel them on PrEP adherence (per national guidelines), test for HIV, and prescribe/dispense PrEP with remote clinician oversight. All participants offered PrEP self-select either daily oral PrEP pills or the DPV-VR. All participants are provided with a study phone number to call free of charge for clarifying questions or concerns with PrEP use (Fig. 3).

**Fig. 3 Fig3:**
[figure not shown]
PrEP pathway in randomization arms. AGYW, adolescent girls and young women; HIV, human immunodeficiency virus; PrEP, pre-exposure prophylaxis [23]

Pharmacies randomized to the nurse navigator model receive tailored support counseling in addition to standard PrEP services. Support counseling by nurse navigators provides educational messaging tailored to AGYW and actionable advice targeting PrEP persistence and adherence and/or FP topics and addresses participants’ questions related to the content at each study visit. Counseling includes adherence encouragement (IMB domain: motivation), PrEP efficacy and safety (IMB domain: information), self-efficacy for prevention of HIV, support for potential PrEP side effects, behavioral skills (tips for remembering PrEP medications, IMB domain: behavioral skills), and strategies for remembering PrEP refill schedules (Fig. 1). All participants receive PrEP adherence counseling per Kenyan national guidelines.

### Criteria for discontinuing or modifying allocated interventions 

N/A. Study participants can decline or discontinue PrEP at any time, and PrEP use is not a criteria for study participation. The nurse navigator intervention is allocated at the pharmacy-level and therefore cannot be discontinued or modified.

### Strategies to improve adherence to interventions 

N/A. The nurse navigator intervention is allocation at the pharmacy-level and therefore individual study participant adherence to the intervention is not required.

### Relevant concomitant care permitted or prohibited during the trial 

The study participants are permitted to seek services within the study sites or in any other healthcare facility without being penalized whatsoever.

### Provisions for post-trial care 

The study will prioritize the safety of the study participants as per ethical requirements. If a participant requires medical care that the study cannot provide, the study clinicians will refer participants to the appropriate services or organizations that can provide care. In cases of adverse events whether related to study participation or not, we will refer them for proper management. If a participant seroconverts while on PrEP, we will ensure they are referred to the HIV care clinic for confirmatory testing and linkage to care as per the national guidelines. The study provides comprehensive PrEP training to the pharmacy providers and nurses delivering PrEP to ensure they can continue to provide PrEP services post-trial.

### Outcomes 

Our primary outcome is PrEP initiation among AGYW seeking contraception at retail pharmacies at enrollment and evidence of self-reported use at 1-month post-use (Table 1). Our second primary outcome is PrEP persistence at 10 months among AGYW who initiated PrEP. Our third primary outcome will be PrEP adherence defined as either TFV or DPV hair levels (depending on PrEP method) at 10 months.

**Table 1 Tab1:** Primary, secondary, and exploratory outcomes of the trial

Outcome		Definition
Primary	PrEP initiation	Binary endpoints (yes, no) of self-reported use of oral PrEP or DPV-VR at 1 month after acceptance at enrollment. Self-reported PrEP use will be considered initiation. If a participant declined or reported not using PrEP after acceptance, the participant will be considered non-initiated
	PrEP persistence	Binary endpoints (yes, no) of self-reported use of oral PrEP or DPV-VR at 10-month after acceptance at enrollment. Self-reported PrEP use will be considered persistence. If a participant declined PrEP or reported not using PrEP after acceptance or discontinued PrEP before 10 months will be considered non-persistent [24]
	PrEP adherence	Binary endpoints (yes, no) of detectable TDF levels in hair > 0.038 ng/mg or DPV levels > 0.0248 n/mg at 10-month visit will be considered adherent. If a participant stopped PrEP use or exited study before 10 months (i.e., no hair sample collected), the participant will be considered non-adherent
Secondary	PrEP method selection	Binary endpoints (yes, no) of self-reported DPV-VR compared to daily PrEP when offered at enrollment
	Predictors of non-adherence	Factors associated with poor adherence (< 90% adherent on PrEP or discontinuation) will include demographics, relationship/partner characteristics, psychosocial factors, socio-economic status, low health/HIV literacy, fear of disclosure
	STI incidence and cofactors	Frequency of STI (syphilis, gonorrhea, and chlamydia) detection at follow-up will be compared between randomization arms
Exploratory	HIV incidence	Frequency of HIV diagnosis at follow-up visits will be compared between randomization arms
	Quality of care	Binary endpoints (yes, no) based on MEASURE Evaluations indicators for quality of care in family planning (e.g., Did the provider ask if you were having a problem with your FP method?)
	Contraceptive method mix	Binary endpoints (yes, no) or LARC use will be compared between randomization arms and distribution of contraceptive method types

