### Sample size 

To account for between-cluster variability, sample size calculations incorporated the coefficient of variation between pharmacies (*k*) [25, 26]. Assuming each cluster enrolls 95 (accounting for 15% attrition) AGYW and that 30% of participants achieve the primary outcome of PrEP persistence at 10 months (31) in the standard pharmacy PrEP model arm (control arm) arm with a coefficient of variation between clinics (*k*) of 0.05, 10 clusters per arm will give 90% power to detect a 15% absolute difference in proportions and a two-sided test with *α* = 0.05. Typical (*k*) values are 0.15 to 0.5 for rare binary outcomes and 0 to 0.05 for non-rare outcomes [25, 26]. Assuming 15% attrition, will enroll a final sample of 1900 ANC attendees at 20 sites (95 women per site; 950 women per arm).

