## Statistical methods

### Statistical methods for primary and secondary outcomes 

We will conduct an intention-to-treat analysis with the primary exposure of randomization arm (pharmacy-based PrEP delivery with nurse navigators vs. standard pharmacy-based PrEP delivery without nurse navigators) to test the hypotheses that incorporating nurse navigators within a pharmacy-based PrEP delivery model will improve PrEP initiation, persistence, and adherence among AGYW seeking contraception at retail pharmacies.

For analyses of our primary outcomes, we will use a log-binomial regression model to estimate relative risks and 95% CI. We will include any imbalanced baseline demographic, clinical, or behavioral characteristics between arms as independent variables in an adjusted model. If primary outcome data are missing or in cases of loss to follow-up, we will assume PrEP discontinuation/nonadherence to fit the most conservative models.

Secondary outcome analyses will include PrEP method selection, predictors of non-adherence, and STI incidence and cofactors. For data analysis approaches, we will use log-binomial regression with robust standard errors for the former two and Anderson-Gill survival analysis for the later. Exploratory analyses will include HIV incidence, quality of care, and contraceptive method mixed by randomization arms (Table 1). We will use survival analysis, generalized estimating equation models with logistic link, and robust standard errors and log binomial regression respectively.

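### Three primary outcomes are declared with initiation listed first, but the trial is sized on persistence alone at the full two-sided 0.05, and no ranking or success rule is stated

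*Protocol article*

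**What the plan says.** The abstract (Methods) lists three primary outcomes side by side: "The primary trial outcomes are PrEP initiation (use of PrEP at 1 month), persistence (use of PrEP at 10 months), and adherence". Table 1 also groups all three as primary.

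The Outcomes section numbers them. It begins "Our primary outcome is PrEP initiation among AGYW seeking contraception at retail pharmacies at enrollment and evidence of self-reported use at 1-month post-use", continues "Our second primary outcome is PrEP persistence at 10 months among AGYW who initiated PrEP", and ends "Our third primary outcome will be PrEP adherence defined as either TFV or DPV hair levels".

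The Sample size section works with one outcome only. It assumes that "30% of participants achieve the primary outcome of PrEP persistence at 10 months" in the control arm and states that "10 clusters per arm will give 90% power to detect a 15% absolute difference in proportions", with a "two-sided test with *α* = 0.05". This is the only significance level given for the primary outcomes.

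Statistical methods for primary and secondary outcomes sets out an intention-to-treat comparison "to test the hypotheses that incorporating nurse navigators within a pharmacy-based PrEP delivery model will improve PrEP initiation, persistence, and adherence". One log-binomial model with 95% confidence intervals serves the primary outcomes. The article states no testing order, division of alpha or rule for declaring the trial positive.

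**The concern.** A reader cannot tell whether the trial succeeds on any one primary outcome, only on all three, or on persistence with the others in support. The two places that come closest to an answer point to different outcomes: Outcomes puts initiation first, while Sample size gives the full alpha to persistence.

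The choice matters because the three outcomes are not equally strong evidence. Initiation is self-reported use at 1 month, collected by study-staff questionnaire in an unblinded trial. Adherence is the only one measured by drug level in hair. As the article stands, a gain in self-reported use at 1 month could be presented as a positive primary result even if 10-month persistence, the outcome the trial was sized for, and hair levels showed nothing.

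**Working it through.** **1. The plan's own figure.** Inputs from Sample size: control 30%, difference 15 points (so 45%), 10 clusters per arm, 95 women per cluster, k = 0.05, two-sided 0.05, power 90%. The usual coefficient-of-variation formula is

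c = 1 + (z_α/2 + z_β)² × [p0(1−p0)/m + p1(1−p1)/m + k²(p0² + p1²)] / (p0 − p1)².

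- With m = 95, the bracket is 0.21/95 + 0.2475/95 + 0.0025 × 0.2925 = 0.00555.
- Clusters needed for 90% power: 1 + 10.507 × 0.00555/0.0225 = 3.6 per arm.
- With 10 clusters: √(9 × 0.0225/0.00555) − 1.96 = 6.04 − 1.96 = 4.08, so power is above 99.9%. Removing 15% attrition (m = 80.75) leaves it above 99.9%.

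The stated 90% is therefore not reproduced from k = 0.05. It is nearly reproduced if 0.05 was meant as k² (k = 0.224): the bracket becomes 0.01944 and power is 89.8% (88.5% at m = 80.75). The text does not say this. It is a separate matter, and enters here only through the cost of a remedy in step 5.

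**2. Error rate if any one success counts: limits.** Suppose each of three null outcomes is tested at two-sided 0.05.

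- Either direction, independent tests: 1 − 0.95³ = 14.3%; upper bound 3 × 5% = 15%.
- False benefit, independent tests: 1 − 0.975³ = 7.3%; upper bound 3 × 2.5% = 7.5%.

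**3. Allowing for correlation.** The document gives no correlation between the outcomes, so a range is assumed. Trivariate normal probabilities:

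| Common correlation | Either direction | False benefit |
|---|---|---|
| 0 | 14.3% | 7.3% |
| 0.5 | 12.5% | 6.3% |
| 0.8 | 9.8% | 4.9% |
| 0.9 | 8.4% | 4.2% |

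**4. Nested outcomes.** Table 1 counts women who declined or stopped as failures on the later outcomes, so the three are roughly nested. For nested binary outcomes with rates a > b, the correlation is √[b(1−a)/(a(1−b))]. Only the 30% persistence rate is the trial's planning figure; the other rates are assumptions.

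- At 60%, 30% and 15%, the correlations are 0.53 (initiation and persistence), 0.34 (initiation and adherence) and 0.64 (persistence and adherence). The error rate is 12.3% in either direction and 6.2% for false benefit.
- Over five other sets (initiation 50% to 85%, adherence 5% to 20%), it is 11.8% to 13.8% in either direction and 5.9% to 6.9% for false benefit.

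Nesting needs a common denominator, as in Table 1. The Outcomes text instead restricts persistence to women who initiated, and the formula would not then apply. The wider range in step 3 does not rely on nesting.

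**5. What an adjustment would cost persistence.** Holm tests the smallest p-value at 0.05/3 = 0.0167, which is the strictest level persistence could face. At that level (z = 2.394):

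- with k = 0.05, power stays above 99.9%;
- with k² = 0.05, it is Φ(3.227 − 2.394) = 79.8% (77.8% at m = 80.75).

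Testing persistence first in a fixed order keeps it at 0.05, so its power is unchanged on either reading.

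**The case against.** Three points can be made for the plan.

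First, a reader might infer that the document contradicts itself on which outcome is primary. It does not. The abstract, Outcomes and Table 1 all declare three primaries, and persistence is one of them. Sizing a trial on one of several primaries is ordinary practice. What is left unclear is the ranking: singular wording is attached to initiation in one section and to persistence in another.

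Second, a statistical analysis plan is mentioned under Interim analyses but is not shown, and multiplicity rules are often placed there. That is fair, and the absence of an adjustment from an article is weak evidence by itself. The mismatch between Outcomes and Sample size, however, is visible in the article and should be settled there.

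Third, the article nowhere says that one success is enough. The hypotheses are joined by a conjunction, which could mean that all three must succeed, and then there is no inflation. This stands, and the error rates above are conditional for that reason. But the wording equally allows three separate hypotheses, each claimed on its own.

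A reader might also take 12% to 14% as the chance of falsely claiming that navigators help. Those figures include significant results favouring the control arm. False benefit cannot exceed 7.5%, to be set against a nominal 2.5%.

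**Conclusion.** The concern holds as a problem of ranking and success rule that should be corrected. Three primaries are declared with initiation first, the trial is sized on persistence at the full 0.05, and nothing says which result makes the trial positive.

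If any one success counts, the error rate is about 8% to 14% in either direction (nominal 5%) and about 4% to 7% for false benefit (nominal 2.5%). If all three must succeed, there is no excess. The ranges assume correlations from 0.9 down to 0, normal test statistics, and tests that hold their nominal level with 20 clusters.

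The numbering in Outcomes could be read as a testing order. Error would then be controlled, but persistence could be claimed only after initiation had succeeded, so the power stated for persistence would be a ceiling.

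**What to change.** Make Outcomes and Sample size agree on the standing of the three outcomes, and state the success rule. Either of these would do:

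- **Fixed order**, each test at two-sided 0.05, stopping at the first non-significant result. Persistence, the powered outcome, goes first; the sponsor chooses the order of adherence and initiation.
- **Holm** across the three, if no order is wanted.

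If the intention is that all three must succeed, saying so also settles the matter, and no adjustment is then needed.

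The text change is short, but it is more than editorial. Under a fixed order, an outcome placed later, including initiation, cannot be claimed as confirmatory if an earlier one fails. Holm would cost persistence some power if the true between-pharmacy variation exceeds the stated k = 0.05: down to about 78% to 80% at the strictest step if 0.05 was meant as k². Because recruitment began in May 2023, the choice should be dated and made by people who have not seen outcome data by arm.

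### Persistence, the outcome the trial is powered on, has two incompatible denominators, and the initiators-only one conditions on another primary outcome

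*Protocol article*

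**What the plan says.** The Outcomes section of the protocol article defines persistence twice.

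- **Narrative:** "Our second primary outcome is PrEP persistence at 10 months among AGYW who initiated PrEP".
- **Table 1, persistence row:** "If a participant declined PrEP or reported not using PrEP after acceptance or discontinued PrEP before 10 months will be considered non-persistent".

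The initiation row of Table 1 describes the same women as non-initiators: "If a participant declined or reported not using PrEP after acceptance, the participant will be considered non-initiated".

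Other sections bear on the choice:

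- **Statistical methods for primary and secondary outcomes:** "We will conduct an intention-to-treat analysis with the primary exposure of randomization arm". The hypothesis is that navigators "will improve PrEP initiation, persistence, and adherence among AGYW seeking contraception at retail pharmacies". Missing outcomes and losses to follow-up are taken as discontinuation or non-adherence. The section on missing data repeats this rule.
- **Sample size:** the control rate is that "30% of participants achieve the primary outcome of PrEP persistence at 10 months". Each pharmacy enrols 95 women, and the only allowance is for 15% attrition.
- **Criteria for discontinuing or modifying allocated interventions:** "PrEP use is not a criteria for study participation".
- **Abstract:** persistence is given as PrEP use at 10 months, with no restriction to initiators.

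**The concern.** A woman who declines PrEP at enrolment is outside the persistence analysis under the narrative and a failure inside it under Table 1. These are different estimands: persistence given initiation, and being on PrEP at 10 months among all women enrolled.

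Only the second keeps the randomised comparison. Initiation happens after the pharmacies are randomised, and the intervention is meant to change it. If navigators lead more hesitant women to start, the initiators in the two arms are no longer comparable. The conditional rate in the navigator arm can then fall even while more of its enrolled women are on PrEP at 10 months.

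The narrative also weakens the missing-data rule. If that rule is applied to the 1-month outcome, a woman lost before month 1 becomes a non-initiator. The narrative would then drop her from persistence, although the plan intends to count her as a failure.

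**Working it through.** **1. Are the definitions compatible?** Table 1 places women who declined, or reported no use after acceptance, in both the non-initiated and the non-persistent groups. Under the narrative these women have no persistence outcome. So the definitions conflict. Table 1 does not use the words all enrolled; that follows from counting decliners as failures.

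**2. The plan's own figures.** 20 × 95 = 1900 reproduces the total, and 95 × 0.85 = 80.75, about 81 evaluable women per pharmacy. No reduction is made for non-initiation.

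For power I used the cluster formula with a coefficient of variation:

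power = Φ( √[(c − 1)(p1 − p0)² / v] − 1.96 ), with v = [p0(1 − p0) + p1(1 − p1)]/n + k²(p0² + p1²)

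Sample size gives p0 = 0.30, an absolute difference of 0.15 (read as p1 = 0.45, an improvement), k = 0.05 and c = 10 per arm. With n = 81:

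- v = 0.4575/81 + 0.0025 × 0.2925 = 0.00638
- √(9 × 0.0225/0.00638) = 5.63
- power = Φ(3.67), about 99.99%

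The stated 90% is therefore not reproduced from the stated inputs. That is a separate matter and this point does not depend on it.

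**3. What the initiators-only version would show.** Under Table 1 a woman who declined or did not use PrEP cannot be persistent, so every persister is taken to be an initiator. Then:

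persistence among initiators = persistence among all enrolled / proportion initiating

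Inputs are 30% and 45% among all enrolled (Sample size) and 85% initiation with a navigator (pilot, Background and rationale). Control-arm initiation is not given, so it is an **assumption**, shown from 40% to 85%. Navigator arm: 0.45/0.85 = 52.9%.

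| Assumed control initiation | Control persistence among initiators | Navigator minus control |
|---|---|---|
| 40% | 0.30/0.40 = 75.0% | -22.1 points |
| 50% | 0.30/0.50 = 60.0% | -7.1 |
| 56.7% | 0.30/0.567 = 52.9% | 0 |
| 60% | 0.30/0.60 = 50.0% | +2.9 |
| 70% | 0.30/0.70 = 42.9% | +10.1 |
| 85% | 0.30/0.85 = 35.3% | +17.6 |

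Every row has the same 15-point benefit among all enrolled women.

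**4. When the sign changes.** It reverses when navigator initiation divided by control initiation exceeds 0.45/0.30 = 1.5. With 85% in the navigator arm, that means control initiation below 0.85/1.5 = 56.7%. A smaller overall benefit reverses more easily: 30% vs 40% reverses below 0.85 × 0.30/0.40 = 63.8%, and 30% vs 35% below 0.85 × 0.30/0.35 = 72.9%.

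**5. Does the smaller denominator cost power?** Holding 30% vs 45% and k = 0.05, and changing only n:

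- 81 × 0.85 = 69 initiators per pharmacy: 99.95%
- 81 × 0.60 = 49 per pharmacy: 99.4%

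**The case against.** The best defence is that one narrative sentence is loose drafting. Table 1, the intention-to-treat statement, the failure rule for missing outcomes and the abstract mostly favour all enrolled women, and an analysis plan that is not shown may already say so. Much of this stands, and it is why the fix is easy. It does not remove the contradiction, because the narrative sentence is explicit and nothing in the article ranks it below the table. The sample-size support is suggestive rather than decisive: the 30% rests on a cited source, and the article does not say whether that rate was among initiators or all women.

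Three stronger readings are tempting, and the documents do not support them.

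- **That the initiators-only result will reverse.** This depends on control initiation, which is not given. At 60% control and 85% navigator initiation, the design effect still gives a positive difference of 2.9 points.
- **That the trial loses power by dropping non-initiators.** At the stated k = 0.05 it does not, as step 5 shows.
- **That women testing HIV-positive would be enrolled and scored as non-initiators.** A reader might infer this because the objective concerns "PrEP initiation, persistence, and adherence among HIV-negative AGYW" while the listed criteria ask only for willingness to be tested. No section says such women are enrolled or how they are scored, and a condensed article may leave that handling to the full protocol.

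It would also be conjecture to say that the denominator will be chosen after results are seen.

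**Conclusion.** The definition of persistence is wrong as written: the Outcomes section gives two denominators that cannot both apply. The initiators-only version conditions on a post-randomisation primary outcome, conflicts with the stated intention-to-treat analysis, and loses randomised comparability whenever initiation differs by arm.

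At the design effect, the initiators-only difference runs from about -22 to +18 points as assumed control initiation goes from 40% to 85%, against a fixed 15 points among all enrolled. This range rests on the pilot's 85% carrying over to the navigator arm and on every 10-month persister being an initiator. The contradiction and the intention-to-treat argument need neither assumption.

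**What to change.** In the Outcomes narrative, delete the restriction to women who initiated PrEP. State that persistence at 10 months is analysed in all enrolled women according to the arm of their pharmacy. Women who declined, did not use or discontinued PrEP count as non-persistent, as in Table 1. Women lost to follow-up count the same way, as in the two statistical sections that set the missing-data rule. Report persistence among initiators by arm as descriptive only, without a test of the navigator effect.

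The cost is a change of wording. It needs no new data, visits or change in sample size. Recruitment has begun, so if the change is handled as an amendment it goes through the ethics approvals that the article describes. It should be dated before outcomes are examined by arm.
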